### Data Management

The collection of the audit data is performed on paper. The registration templates will be stored securely in in each participating nursing home and will be accessible only by study staff and authorized personnel. Charts will be transferred electronically to the Audit Project Odense service provider to be entered in a database [31]. Data from residents will be anonymously collected from the beginning and no identifiable or personal information will be gathered. Nursing homes will be identified by a code. Qualitative interviews will be audio recorded, transcribed, and translated, and any identifiable information will be deleted in the process. Translations will be transferred securely to the organization in charge of analyzing the results. Anonymized data from the survey will be stored for a minimum of 5 years after publication of the results. Anonymized project data will be shared for common analyses and presentation to the scientific community through publications and conferences.

### Ethical Considerations

The study is conducted in accordance with the protocol, the Declaration of Helsinki, the principles of Good Clinical Practice, The General Data Protection Regulation (of the European Union) 2016/679 and the Human Research Act as well as other locally relevant regulations. Appropriate regulatory or ethical approval has been sought in each of the countries taking part in the study, and all study procedures started after gaining approval on the basis of the master protocol, translated where necessary to local language. In Spain, the coordinating country, the study protocol was approved by the Ethics Committee of Institut Universitari d’Investigació en Atenció Primària (IDIAP Jordi Gol), Institute of Research in Primary Health Care (23/080-P).

Nursing homes have been contacted by local coordinators that have explained the study and handed over the information, giving the nursing home time to read it and ask any questions. Informed consent was obtained from all participants. HCPs are participating voluntarily in this quality improvement project. No personnel data are collected from either HCPs or patients. A nursing home can withdraw from the project at any time without giving any explanation. The information gathered from the residents’ prescriptions are personally nonidentifiable data and we are collecting the minimum data set necessary for the study. Data are anonymized from the beginning, coded in the template with the code of the nursing home and a consecutive number for each antibiotic treatment. Individual patient consent is therefore not required.

## Results

The local coordinators in each of the countries have already contacted all the nursing homes participating in the IMAGINE project, with a total of 109 nursing homes. All these nursing homes have already completed the first audit registration. The results of the first audit registrations will be available before the intervention takes place in November 2024. The overall results of the IMAGINE project will be available after summer 2025 and the results will be published by the end of 2025.

## Discussion

We hypothesize that this 2-day multifaceted intervention for health care providers in nursing homes will significantly improve adherence to IPC practices and enhance understanding of when to suspect a UTI. This improved adherence is expected to result in a notable reduction in the rates of inappropriate antibiotic consumption for UTIs. We anticipate that these changes in practices and antibiotic usage will be followed by a subsequent reduction in the incidence of UTIs, as observed during the second registration audit. The overall aim is to enhance the quality of care and patient outcomes through better preventive measures and more judicious use of antibiotics in nursing homes.

The increasing concern about the emergence of AMR in nursing homes necessitates a cohesive and systematic approach to address challenges across very heterogenous settings and diverse health care delivery systems, already under pressure. Additional challenges result in a confluence of risks for colonization or infection with multidrug-resistant pathogens among residents, rendering nursing homes potential reservoirs for AMR [34]. Infections caused by antibiotic-resistant bacteria are associated with a greater need for medical visits; more hospital admissions; higher mortality; and higher economic, intersectoral, and societal costs [35,36]. A recent study tested a multifaceted AMS stewardship intervention in Poland, the Netherlands, Norway, and Sweden and found it effectively and safely reduced UTI antibiotic prescriptions among frail older adults [37]. This study demonstrates that educating care home staff about UTIs and improving their communication with HCPs significantly reduces inappropriate UTI antibiotic prescribing [38,39]. This high use of UTI antibiotics in care homes may be driven by a high prevalence of asymptomatic bacteriuria among residents, which can be as high as 50%, compared to just 4% in older people living independently [40,41]. This is despite no reported benefit from treating asymptomatic bacteriuria with antibiotics. Clinical uncertainty around symptoms such as confusion, falls, and agitation being attributed to UTIs also contributes to the high rate of antibiotic use [42].

Implementing hygiene strategies and reducing the unnecessary prescription of antibiotics has been shown to be the most effective measure to curb the problem of AMR [43,44]. The IMAGINE study aims to address gaps related with AMS and IPC elements through an intervention targeting HCPs to enhance their adherence to good clinical practices. Importantly, this study poses no risks to the HCPs or the residents whose treatment data will be collected. The intervention will use various techniques, including providing feedback to HCPs in nursing homes, conducting follow-up meetings, facilitating discussions on guidelines, offering training courses for HCPs with special focus on when a UTI should be suspected, and distributing informative and educational materials to residents and their relatives.

Furthermore, the IMAGINE study encompasses 8 European countries that exhibit diverse prevalence of antibiotic resistance, distinct cultural backgrounds, varying socioeconomic indices, and different health care systems. This broad scope increases the applicability of the study findings to a wide range of settings. If we find our intervention to be effective, we strongly believe this work has great potential for dissemination. The final results of this quality improvement project will be submitted for publication in a peer-reviewed journal and presented at international scientific conferences. Ultimately, these findings will inform public health interventions aimed at promoting appropriate antibiotic prescribing and implementing effective hygiene strategies in nursing homes.

The use of the Audit Project Odense method has certain limitations. The one notable weakness is the lack of external validity associated with the collected data. Since nursing home HCPs participate voluntarily, their prescribing habits may not accurately represent the average antibiotic use in all nursing homes within their country. Additionally, the nursing homes involved in the audits might exhibit a greater interest in quality improvement and potentially use more rational antibiotic practices compared to nonparticipating nursing homes [45]. Another aspect to consider is the potential influence of conducting an audit on providers’ prescribing behaviors. The HCPs are aware of being observed, which can lead to what is known as the Hawthorne effect. It is important to note that this study is not a clinical trial and lacks a control group, which could be considered a limitation. However, the study will compare the same participants before and after the intervention. Participation in a quality improvement project can pose a barrier due to the required time commitment. While completing a registration takes less than 2 minutes, HCPs need to allocate time for educational courses and other planned activities associated with the intervention. Another weakness is the cross-sectional nature of the Audit Project Odense method. The variables included in the registration chart are aligned with the consultation process, and ideally, the decision to treat should follow the establishment of a diagnosis. However, in practice, diagnostic procedures and treatment decisions are often intertwined [46]. HCPs may determine whether to prescribe a medication concurrently or even prior to establishing a diagnosis. Consequently, clinicians may adjust the diagnosis to align with the treatment decision, potentially introducing a diagnostic misclassification bias. Nevertheless, this potential bias would impact the validity of the diagnosis both before and after the intervention, with minimal likelihood of influencing the intervention’s effectiveness. Due to time constraints in the registration process and limitations on the maximum number of columns in the Audit Project Odense chart, only the typical signs and symptoms of UTIs are collected. This may result in certain limitations, as nonbiomedical factors that could serve as powerful predictors of antibiotic prescriptions are not considered in this study. This restricts the definition of antibiotic appropriateness in our study, as it is based on the collected items in the registration charts.

In conclusion, despite the widespread use of antibiotics and the increasing development of AMR, there have been limited efforts to reduce the occurrence of common infections in nursing homes and improve the diagnosis of UTIs. Moreover, there is a lack of initiatives focused on implementing measures related to hygiene and reducing the inappropriate use of antibiotics in this setting. This protocol has summarized the rationale and design of a before-and-after intervention study aimed at evaluating the impact of a multifaceted intervention on antimicrobial use for UTIs among residents in nursing homes, its appropriateness and the elements of hygiene implemented.

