### Project Methodology

A point prevalence audit is scheduled to assess the outcomes of the multifaceted intervention [27]. The audit is conducted in 2 separate 3-month periods: one before the intervention and another after. The initial registration occurred from February 2024 to April 2024, prior to the intervention, while the second registration will take place from February 2025 to April 2025, after the intervention (Figure 1). Throughout the audit, HCPs record anonymized information on UTIs antibiotic prescriptions on a chart. Sometime during the audit registration, participants are asked to also register the IPC measures in place in the nursing homes. Between the first and second audits, participants will attend a multifaceted intervention aimed at improving the prevention and management of infections in nursing homes (November 2024). The intervention and the data collection sheets are specifically designed for the study, based on preliminary work conducted in 2023.

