### Multifaceted Intervention

Interventions that are expected to have the highest likelihood of success appear to align with the constructs of the normalization process theory, which explain the mechanisms of implementation [28]. These constructs include coherence (making sense of interventions), cognitive participation (engagement with the intervention), collective actions (enabling the intervention to take place), and reflexive monitoring (evaluating the costs and benefits). In the IMAGINE project, the multifaceted intervention aims to address all dimensions of the normalization process theory. It will achieve this by facilitating open discussions regarding variations in practice behaviors and by strengthening communication between HCPs, residents, and their families. Through these efforts, the intervention seeks to enhance the understanding and acceptance of the intervention among all stakeholders involved.

The multifaceted intervention will be composed by face-to-face and web-based activities, the latter in an asynchronous manner, enabling nursing home HCPs to engage in these activities at their own convenience. The main part of the training will be a 2-day intervention program consisting of (1) presentation of the first audit results and discussion with the rest of their colleagues in their respective countries, allowing self-reflection of their performance and discussing quality indicators associated with their practice; (2) AMR and IPC elements, with the participation of national experts; (3) discussion on AMS on how to improve the diagnosis of UTIs and the role of antibiotics for these infections; and (4) discussion of best practice case studies and practical issues.

The courses will be based on active discussion among participants, with the use of videos, leaflets, digital material, and role-playing, allowing fruitful discussion. This intervention will be recorded and adapted to a web-based environment. All material created for the intervention will be used to achieve three main objectives: (1) reinforcing the training of the HCPs, allowing them to revisit concepts whenever they need them; (2) training of the rest of the nursing home staff on IPC measures and AMS; and (3) after the end of the project, training of HCPs in other nursing homes in the country.

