The intervention will be tailored to the nursing home setting. Achieving a significant behavioral change among multiple HCPs is essential for improving antibiotic prescribing in this population. To accomplish this, we will use the participatory action research methodology, which actively involves HCPs in the implementation of IPC and AMS interventions that are customized to their specific health care settings. This approach takes into account the local barriers and facilitators that may affect the successful implementation of these interventions [29]. The primary objective of the participatory action research is to generate practical knowledge that can be readily applied in local practice. By using this methodology, we aim to gain a better understanding of the complex decision-making process related to IPC practices and suspected health care–associated infections among frail elderly residents in nursing homes. It is important to consider the diverse elderly care settings across the various target countries, and participatory action research will help us navigate this heterogeneity [30].

National HCPs and stakeholders will participate to identify factors in the nursing home setting that contribute to increased risk of spread of infection and to determine national characteristics of nursing home management, diagnosis, and antibiotic prescription practices for nursing home residents and elderly patients with symptoms of infection. They will also work together to identify quality improvement areas related to hygiene, infection prevention, and inappropriate use of antibiotics; define priorities to be included when developing the educational material that will be used for facilitating communication between HCPs, residents, and relatives; and define an algorithm to be used for analyzing antibiotic inappropriateness in the different types of health care–associated infections.

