### Data Analysis Plan

The data collected in the specific registration charts have a primary function at the individual level of health professionals, that is, helping them to improve their practice by reconsidering their treatment choices considering clinical evidence, guidelines, and professional consensus [31]. The second function is to analyze the data to evaluate the effect of the intervention. In each audit, data are recorded for all antibiotics prescribed during the 3-month period. We aim to record a minimum of 50 cases in each of the nursing homes recruited (at least 100 nursing homes), yielding an approximate number of 5000 cases in each registration period.

We will apply the chi-square test to determine the frequencies and appropriateness of prescriptions before and after the intervention and Student *t* test for the number of hygiene elements implemented in the nursing homes to test the null hypothesis of no effect of the interventions. To measure the potential reduction in UTIs, we will assume that antibiotics are always prescribed for these infections and every antibiotic is associated with a new episode of UTI [32]. The number of hygiene elements implemented will be compared with a threshold that will be defined during the participatory action research analysis. The appropriateness of antibiotic prescriptions will be defined according to an algorithm based on symptoms and patient characteristics that will be developed at the start of the project. We will also estimate the effect of the interventions on inappropriate prescriptions for UTIs using multilevel logistic regression models with 2 levels: cases and HCP participants, to allow for the fact that patients belonging to the same HCP are not independent of each other [33]. Statistical significance will be considered with *P*<.05. The data will be analyzed using the current version of the Stata statistical program (version 18, StataCorp LLC).

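### Diagnostic misclassification in both audits cancels only if its rate is equal; training the chart-fillers between audits makes a difference likely, so the reassurance in the Discussion does not follow

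*Protocol article*

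**What the plan says.** In its limitations, the Discussion of the protocol article states that "clinicians may adjust the diagnosis to align with the treatment decision, potentially introducing a diagnostic misclassification bias". It then argues that "this potential bias would impact the validity of the diagnosis both before and after the intervention, with minimal likelihood of influencing" the effectiveness of the intervention. The only reason given is that the bias is present in both periods.

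Other parts of the article describe how the outcome data arise:

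- **Who records.** Project Methodology: "Throughout the audit, HCPs record anonymized information on UTIs antibiotic prescriptions on a chart". The Discussion adds that "the study will compare the same participants before and after the intervention", and that there is no control group.
- **How appropriateness is derived.** The Data Analysis Plan uses "an algorithm based on symptoms and patient characteristics". The Discussion says the definition rests on the items collected on the chart, and that only typical UTI signs and symptoms are collected.
- **What happens between the audits.** Participants are shown the first-audit results, "discussing quality indicators associated with their practice" (Multifaceted Intervention). The Discussion lists "offering training courses for HCPs with special focus on when a UTI should be suspected" among the components.

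Reducing inappropriate antibiotic use for UTIs by 40% is one of the primary objectives (Aims).

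**The concern.** Misclassification drops out of a before-after comparison only when it acts at the same rate in both periods. The article gives no reason to expect equal rates, and its design gives a reason to expect unequal ones. The intervention works on the same people, and on the same clinical judgement, that produce the chart entries.

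No bad faith is needed. Staff who have been taught which symptoms point to a UTI may look for them more and tick them more often. A course that the algorithm would have called inappropriate in the first audit can then be called appropriate in the second, although the prescribing decision was the same. The article describes no independent check of chart entries, and there is no control group in which a drift in recording would show.

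At stake is a primary objective. Part of an observed fall in inappropriate prescribing could be a change in charting, and the Discussion tells the reader to disregard that possibility.

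**Working it through.** **Inputs from the article**

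- Cases per audit: 50 per home × 100 homes = 5000 (Data Analysis Plan; the figure reproduces).
- Target: a 40% relative reduction (Aims).
- Significance level: P<.05, taken here as two-sided.

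**Assumptions**

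- Inappropriate share of 60%, and about half of all courses for UTI, so 5000 × 0.5 = 2500 UTI courses per audit. Both come from the survey cited in the Introduction and are not study baselines.
- Relabelling rates and ICCs are mine. The article gives none.

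**Step 1: when does the bias cancel?** Let t0 and t1 be the true inappropriate shares before and after. Let m0 and m1 be the fractions of inappropriate courses recorded with a justifying symptom. The apparent share is t × (1 − m), so

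apparent relative reduction = 1 − (t1/t0) × (1 − m1)/(1 − m0).

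The last factor equals 1 only if m0 = m1.

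| m0 | m1 | No true change (60% → 60%) | True 40% reduction (60% → 36%) |
|---|---|---|---|
| 10% | 10% | 0% | 40% |
| 10% | 20% | 1 − 0.48/0.54 = 11% | 1 − 0.288/0.54 = 47% |
| 10% | 30% | 1 − 0.42/0.54 = 22% | 1 − 0.252/0.54 = 53% |
| 20% | 10% | 1 − 0.54/0.48 = −12.5% | 1 − 0.324/0.48 = 32.5% |

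The first row is the case that the Discussion assumes. The last row is recording that becomes more candid after training; there the bias works against the intervention.

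**Step 2: how little relabelling yields a significant test?** Take m0 = 0, no change in prescribing and n = 2500 per audit, with z = (p0 − p1)/√[2p̄(1 − p̄)/n].

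- m1 = 10%: p1 = 0.60 × 0.90 = 0.54 and p̄ = 0.57. Then z = 0.06/√(2 × 0.57 × 0.43/2500) = 0.06/0.0140 = 4.28, P ≈ 0.00002.
- m1 = 5%: p1 = 0.57 and p̄ = 0.585, so z = 0.03/0.01394 = 2.15, P = .03.
- z reaches 1.96 at about m1 = 4.6% (apparent share 57.2%).

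**Step 3: allow for clustering by home.** The design effect is 1 + (m − 1) × ICC, where m is cases per home.

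| Cases per home | ICC | Design effect | m1 needed for z = 1.96 | z at m1 = 10% |
|---|---|---|---|---|
| 50 | 0.05 | 3.45 | 8.5% | 2.31 |
| 50 | 0.10 | 5.90 | 11.1% | 1.76 |
| 25 | 0.05 | 2.20 | 6.8% | 2.89 |
| 25 | 0.10 | 3.40 | 8.4% | 2.32 |

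Fifty per home is the article's target for all antibiotic cases. If half are UTIs, 2500 courses over 100 homes is 25 per home, so the 50-per-home rows are on the cautious side. The 5% scenario is not significant in any of these rows (z at most 1.45).

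**Step 4: what would explain the whole target?** With m0 = 0 and no true change, an apparent 40% reduction needs m1 = 40%. Modest relabelling can produce a significant result, but only heavy relabelling can produce the full target.

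**The case against.** Several objections have weight.

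- **Direction.** A reader might infer that the bias is shown to favour the intervention. The article does not show that. Knowing which symptoms count makes a favourable shift the more likely one, but more candid recording would reverse it. Either direction contradicts the claim of minimal influence.
- **Diagnosis versus symptoms.** The sentence concerns the validity of the diagnosis, whereas the figures above concern symptom ticks. The distinction is fair. Both are entered on the same chart by the same staff, however, and inferring equality from mere presence in both periods fails for each. The Discussion does list the chart-based definition, the Hawthorne effect and the missing control group as limitations, but it describes the Hawthorne effect in terms of prescribing behaviour, not recording.
- **Existing safeguards.** It would be too strong to say that nothing planned could reveal the problem. UTI episodes are counted from antibiotic courses (Data Analysis Plan), which needs no symptom tick. Infections other than UTI treated with antibiotics are a secondary objective, where UTIs relabelled as another infection could appear. The article does not, however, link these counts to the reading of appropriateness.
- **The algorithm.** Multifaceted Intervention has national professionals and stakeholders "define an algorithm to be used for analyzing antibiotic inappropriateness". A reader might infer that the chart-fillers write the scoring rule or are shown which ticks pass, or that the rule could differ between audits. The article says none of this, and the Data Analysis Plan places development at the start of the project.
- **Magnitude.** The baseline share, UTI share, relabelling rates and ICCs are all assumed, as is zero misrecording at baseline. This stands, so the figures are illustrations and not estimates.

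The hygiene elements are also registered by participants. That is a separate outcome, and the statement at issue does not concern it.

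**Conclusion.** The point holds in a limited form. The Discussion's inference is wrong as written: bias in both audits is harmless to the comparison only at equal rates, and the article both gives no reason for equality and describes an intervention aimed at the people and the judgement behind the data. A difference between audits is likely, and a difference favouring the intervention is probable but unproven.

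Under the stated assumptions, relabelling of roughly one inappropriate course in ten could by itself make the unadjusted test significant, and could bring a clustered analysis to about the threshold. It would produce a 10% apparent reduction, a quarter of the 40% target. The planned multilevel model deals with dependence between cases of the same professional and does not remove this bias. The study can still be run and interpreted; what changes is how firmly a fall in inappropriate prescribing can be attributed to changed practice.

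**What to change.** 1. Delete the statement of minimal likelihood in the Discussion. Say instead that recording may differ between audits because the staff who record are trained in between, and that the direction is uncertain.
2. Report the frequency of each symptom tick by audit.
3. Present the change in appropriateness together with the number of UTI courses and of all antibiotic courses per home per audit. Data Collection and the Data Analysis Plan say that all antibiotic prescriptions are recorded. A falling inappropriate share with unchanged counts would point towards charting. The UTI count is itself open to relabelling as another infection, so the all-antibiotic count is needed beside it. Express these per resident-days only if denominators can be obtained; the article describes none, and the first audit is complete.
4. Add a tipping-point analysis: over a range of m0, find the m1 at which the corrected effect disappears, using the formula in step 1 of the working.

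No new chart fields are needed. The cost is some extra analysis and a more cautious conclusion. Resident-day rates, if wanted, would add retrospective collection of denominators.
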